### Participation timeline

All subjects will be part of the trial for two years post initiation of the treatment or till the time when they show progressive incurable disease.

### Statistical analysis plan

*Sample size calculation*

The sample size is determined by the formula,

n=(Z1−α22)pqd2
, z = Co-efficient of significance (1.96), α = Level of significance (5.0%),

p
= Prevalence of oral tongue tumour (50.0%)

q
 = 1-

p
 (50.0%), d = Desired precision (10.0%).

The minimum sample size for the study is computed and found to be 97 patients.

*Statistical method*

Chi-square Test to test the statistical significance of the association of the molecular expression (severity) of antibodies in lymph nodes and circulating tumor cells as numbers in oral tongue squamous cell carcinoma patients. To find the survival probability of disease-free survival, Kaplan Meier analysis and the comparison will be done using a log-rank test.

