### Study population

The cohort will be adults aged 18-80 years, reporting to the Head and Neck Surgery department of Amrita Institute of Medical Sciences Kochi (tertiary care centre) with histopathological confirmed oral tongue squamous cell carcinoma who has not undergone any other treatment other than diagnostic biopsy, planned for curative intent surgery with neck dissection.

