### Study implementation/methodology

Patient inclusion is done based on the inclusion criteria. The trial will enroll 97 eligible patients. After obtaining written informed consent, blood samples and tissue biopsy blocks will be collected from them.

For CTC/CTM evaluation – Blood samples with minimum trauma will be collected before and 6 months after surgery. 5 mL of peripheral whole blood samples will be collected in 10-mL vacutainer tubes (Becton Dickinson, New Jersey). The blood samples will be stored in the refrigerator at 2 to 8
^0^ C. CTCs will be isolated by using Drugs Controller General of India (DCGI) approved OncoDiscover liquid biopsy technology. The OncoDiscover CTC isolation technique uses multifunctional, iron oxide-based, magneto-polymeric, and anti-epithelial cell adhesion molecule (EpCAM) targeting superparamagnetic nanoparticles.
^
10
^ Enumeration of CTC is based on CD45-, EpCAM+ and CK8,CK18 &CK19+ expression. CTM clusters are a group of two or more aggregated CTCs. The number of CTCs positive for PD-L1 expression is also evaluated.

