## Discussion

Metastasis can even occur many years after surgical resection of primary cancer due to tumor dormancy. Subramaniam N et al
^
5
^ on a study of OTSCC show 20-30% recurrence within 12 months and 40-50% mortality within 5year even after guideline-based treatment. This study showed younger patients had a higher incidence of tongue tumours with increased adverse pathological features.
^
5
^

In the study by Mizrachi et al. 15% of cN0 oral cancer patients developed neck recurrence.
^
6
^ Blatt et al. in their study on tumor recurrence among OSCC, which is one of the largest retrospective studies on oral squamous cell carcinoma described that recurrence is very frequent especially in the first six months after primary tumor diagnosis, they reported approximately 64% with local recurrences.
^
7
^

The new paradigms of metastatic biology research signify that metastasis is not a late onset event in tumor development nor related to tumor volume. Although progress has been made in understanding the mechanism of cancer spread, the complexity of the metastatic process remains a stumbling block.
^
8
^ Cancer cells are dynamic, with greater plasticity and can build their own niches.
^
8
^
^,^
^
9
^ Each cancer cell must be viewed as an organism capable of developing an entire tumour.
^
8
^ Metastasis is a process in which genetic instability of the primary tumor fuels cell heterogeneity, permitting cloning of a few metastatic cells that ultimately emerge and spread the tumour.
^
9
^
^–^
^
11
^

Tumor metastasis is now believed to be closely pursued by prometastatic milieu, premetastatic niche and metastatic niche formation.
^
12
^ Premetastatic niche is an area devoid of tumour cells, but it can nurture cancer cells. It provides a favourable microenvironment for tumour invasion, endurance and/or proliferation of malignant cells later to develop into metastasis.
^
13
^

These are noncancerous changes in a tumor-free organ and may be the most primitive suggestion of metastasis. Lymph nodes have been suggested to offer fertile soil for cancer cell seeding, proliferation, and metastasis.
^
14
^ These act as crucial metastatic spots and are a decisive prognostic parameter in diverse tumor types.
^
15
^
^,^
^
16
^

Primary tumor initiates the sentinel lymph node remodelling by releasing extracellular vesicles, soluble factors, a variety of cytokines, and growth factors before metastasis spread.
^
11
^
^,^
^
17
^

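### The sample size of 97 is derived for the prevalence of tongue tumour, which an all-tongue-cancer cohort cannot estimate, and it does not size the marker and CTC associations with recurrence-free survival

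*Protocol article*

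**What the plan says.** In the protocol article, the sample size paragraph of the Statistical analysis plan section uses the formula for estimating one proportion to a given absolute precision. Its inputs are "z = Co-efficient of significance (1.96"), "α = Level of significance (5.0"%), "Prevalence of oral tongue tumour (50.0"%) and "d = Desired precision (10.0"%). It concludes: "The minimum sample size for the study is computed and found to be 97 patients". The Study implementation/methodology section carries the figure over: "The trial will enroll 97 eligible patients".

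The Study population section restricts entry to adults with "histopathological confirmed oral tongue squamous cell carcinoma", and Table 1 excludes other oral subsites.

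The first two items under Primary outcomes relate RFS to STAT 3, LOX 2 and VEGF expression in tumour-free nodes, and to CTC/CTM at two time points. The third concerns STAT 3 in tissue and PD-L1 on CTCs as indicators of immune status and is not an RFS association. The survival comparison named is Kaplan-Meier with a log-rank test. The sample size paragraph gives no hazard ratio, power, event count, marker split or recurrence rate.

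**The concern.** A sample size calculation should target a quantity that the study estimates or tests. Here the target is a prevalence whose value in the cohort is 100% by design, because only tongue cancers are admitted. There is no wider group of patients from which it could be estimated, and it appears in none of the objectives or outcomes.

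The first two primary outcomes ask whether RFS differs by marker expression or by CTC/CTM status. The information for a log-rank comparison comes from the number of RFS events and from how patients divide between the marker groups. Neither enters the calculation. The recurrence figure that the Discussion does cite, "20-30% recurrence within 12 months", is not used.

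At stake is how the results may be read. If 97 is taken as sufficient for the primary question, a non-significant marker result could be taken as evidence of no association when the study had limited ability to detect one. The Methodological issues section lists limitations but does not mention sample size or power.

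**Working it through.** **1. The stated figure.** With z = 1.96, p = q = 0.5 and d = 0.10, all from the Statistical analysis plan section:

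n = z²pq/d² = 1.96² × 0.5 × 0.5 / 0.10² = 96.04, rounded up to 97. The figure reproduces exactly, so the fault lies in the target and not in the arithmetic.

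**2. What 97 does deliver.** The half-width of a 95% interval for a proportion is 1.96 × √(p(1−p)/n). At n = 97 this is 10.0 points for p = 0.5, 9.1 for p = 0.7 and 8.0 for p = 0.8. Since p = 0.5 is the worst case, 97 fully observed patients estimate any single proportion, such as two-year RFS or the CTC-positive share, to within about 10 points.

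**3. What 97 delivers for the RFS associations.** The documents give no two-year event rate, marker split, target hazard ratio or power, so the following are assumptions: 20%, 30% or 40% of the 97 patients with an RFS event by two years; marker groups of 50:50 or 30:70; two-sided 5%; 80% power. The nearest figure in the article is the 12-month recurrence quoted above. With D events and a share π in one group, Schoenfeld's approximation gives:

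- detectable HR = exp[(1.96 + 0.8416) / √(D π(1−π))]
- power for HR 2.0 = Φ(ln 2 × √(D π(1−π)) − 1.96)

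For example, D = 29 and π = 0.5 give √7.25 = 2.693, so the detectable HR is exp(2.8016/2.693) = 2.83, and power for HR 2.0 is Φ(0.693 × 2.693 − 1.96) = Φ(−0.09) = 46%.

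| Event rate (assumed) | Events | Detectable HR, 50:50 | Detectable HR, 30:70 | Power for HR 2.0, 50:50 |
|---|---|---|---|---|
| 20% | 19 | 3.6 | 4.1 | 33% |
| 30% | 29 | 2.8 | 3.1 | 46% |
| 40% | 39 | 2.5 | 2.7 | 58% |

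Conversely, 80% power for HR 2.0 at a 50:50 split needs (1.96 + 0.8416)² / [(ln 2)² × 0.25] = 65.3, so 66 events. That would be 66/97 = 68% of the cohort.

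**4. The N0-only objective.** The Introduction restricts the secondary CTC/CTM objective to N0 patients, while Table 1 admits patients with and without nodal metastasis. If 50%, 60% or 70% of the 97 are N0 (assumed; about 48, 58 or 68 patients), the worst-case half-width is 14.1, 12.9 or 11.9 points, wider than the 10 points in the plan.

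**The case against.** The strongest reply is that p = 0.5 is the usual conservative value, so 97 serves any proportion whatever the label says. This stands in part: the number is a valid precision target for a single proportion, and the article does plan to determine RFS at two years. It would therefore go too far to say that 97 has no bearing on RFS. But the article does not make that argument. It names a specific prevalence, and precision for one proportion does not size a comparison of RFS between marker groups.

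A second reply is that a full protocol or a separate analysis plan may hold more. That would excuse missing detail. Here the article states its basis outright, and for a quantity the study cannot estimate.

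Some stronger readings are tempting but not supported:

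- A reader might infer that the primary marker analysis is confined to N0 patients, with far fewer events. In the primary objective, N0 describes tumour-free nodes. The text accompanying Figure 1 takes uninvolved nodes from node-positive patients as well, so the analysis can draw on most of the cohort. Only the secondary CTC objective is limited to N0 patients. A detectable hazard ratio for that subgroup would rest on several stacked assumptions and possibly very few events, so none is given.
- A reader might trace the 50% to the Introduction's share of oral cancers arising in the tongue and floor of mouth. The article does not give the source, and the value may simply be the conventional default.
- A reader might say that the article claims adequate power. It does not. That a null result would be misread is a risk, not something the text asserts.

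**Conclusion.** The point holds. The stated basis for 97 is wrong as written: it targets a prevalence that is fixed by the entry criteria and that no outcome uses. The number gives about ±10 points for any single proportion in the full cohort and, if 50–70% of patients are N0, about ±12 to ±14 points for the N0-only objective.

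For the marker and CTC/CTM associations with RFS, the study would have 80% power only for hazard ratios of roughly 2.5–3.6 at an even split and 2.7–4.1 at 30:70. At an even split it would miss a true doubling of the hazard between about 42% and 67% of the time. These figures rest on assumed two-year event rates of 20–40% and assumed marker splits. They are illustrations, and no single corrected sample size follows from the documents. The finding about the mislabelled target does not depend on them.

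**What to change.** Keep 97 and change the justification:

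- Delete the reference to the prevalence of oral tongue tumour.
- Have the sponsor state the true basis for 97, for example ±10 points for a named proportion that the study will estimate, or feasibility if that is the reason. The article does not say which, so the review should not supply one.
- Add the expected number of RFS events and the hazard ratio detectable with 80% power, with the assumed event rate and marker split shown.
- Give the wider precision that applies to the N0-only CTC/CTM objective.
- Report the marker and CTC/CTM associations with RFS as estimates with confidence intervals, and state that a non-significant result does not exclude hazard ratios below the detectable value.

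The cost is wording only, with no extra patients. The downside is that the study's stated capability becomes less favourable. The Study status section reports 27 patients recruited and nodal marker evaluation not yet begun, so at that stage the change could be made before any marker results existed.

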**Figure 1. f1:**
[figure not shown]
Trial Design of PMN Study.

The lymph nodes collected for analysis will include nodes without disease both in groups, where there is no nodal disease (-ve LN in NO) and those with nodal disease (-ve LN in N+). Also, will include lymph nodes with disease (LN+) and those with ECS (LN++). The molecular markers studied in the lymph nodes will be STAT 3, LOX 2, and VEGF A. IHC technique to be employed with primary and secondary antibody standardization protocol.

Group A: First echelon lymph nodes will be sampled in pathologic N0 (-ve node in NO).

Group B: In node-positive cases, - a normal uninvolved lymph node is taken just distal to the level of lowest positivity ie. if level 2 is involved, an uninvolved node from level 3 is taken (B1). The lymph nodes with positive disease (B2) and those with extracapsular spread (B3) will be included in the analysis when present.

To investigate the molecular characteristic features in the formation of premetastatic lymph nodes, selecting nonmetastatic LNs in the vicinity of metastatic LNs seems to be most suitable. Being taken from the same patient most of the other variables can be avoided.

The preparation of slides will be done in accordance with standard IHC techniques. Manual IHC with antigen retrieval in pressure cooker will be done. All antibody standardization will be done according to the company protocol manual. All stained slides shall be photomicrographed within 48 hours. Interpretation will be performed independently by two pathologists who were blinded to the other parameters of the subject. In cases of disparity, a third pathologist will be consulted and the best concordant result will be accepted for analysis. IHC slides will be graded according to staining intensity. The patients will be followed up as per the standard of care ie 2 monthly for the first year and 3 monthly in the second year. Clinical evaluation supplemented by imaging if needed will be used during follow-up. The overall survival, recurrence-free survival, locoregional, and systemic failure rates will be determined at the end of two years follow-ups.

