### Primary outcomes

•The correlation of molecular expression of STAT 3, LOX 2, and VEGF in the premetastatic nodes (-ve N) with recurrence -free survival. These markers will be correlated individually. This will allow us to analyse the significance of premetastatic niche formation and the pathways leading to it.•To correlate the presence of CTC/CTM at two different time points to recurrence-free survival. This will allow us to establish the role of liquid biopsy in prognostication ie. the presence of CTC as a predictor/indicator of tumor spread via blood or lymphatic channels.•The evaluation of Stat3 expression in tissue and PD- L1 in CTC will reveal on the local and systemic immune status of patients respectively. Those PD-L -1positive CTCs may be a strong indicator of those exceptional CTCs that escape the immune surveillance mechanism.

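### The only survival test named ignores the order of the staining grades; a log-rank test for trend would use it at almost no cost

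*Protocol article*

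**What the plan says.** The Primary outcomes section relates the expression of STAT 3, LOX 2 and VEGF in tumour-free nodes to recurrence-free survival, one marker at a time: "These markers will be correlated individually". The Immunohistochemistry section fixes the scale: "IHC slides will be graded according to staining intensity". It does not give the number of grades.

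The Statistical method paragraph has two sentences. The first assigns a chi-square test to the "association of the molecular expression (severity) of antibodies in lymph nodes and circulating tumor cells as numbers". The second covers survival: "Kaplan Meier analysis and the comparison will be done using a log-rank test". No trend test and no regression model is named.

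For circulating tumour cells (CTC) and clusters (CTM), the survival outcome is worded as presence: "To correlate the presence of CTC/CTM at two different time points to recurrence-free survival".

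**The concern.** Staining grades have an order, and the primary question is whether recurrence-free survival falls as expression rises. A log-rank test across *k* grades, in its usual form, asks only whether the *k* curves differ in any way. It has *k* − 1 degrees of freedom and gives the same result however the grades are relabelled. If risk climbs with grade, part of the information is lost.

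The loss matters because the sample size was not derived from any survival comparison, so there is no planned reserve of power to spend. If the all-grade test looks weak, it also becomes tempting to collapse the grades into high and low after seeing the curves.

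**Working it through.** **1. The protocol's own figure.** n = z²pq/d² = 1.96² × 0.5 × 0.5 / 0.10² = 96.04, rounded up to 97. The stated figure is reproduced. It is a precision calculation for one proportion. It contains no hazard ratio, event count or power for recurrence-free survival.

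**2. Number of recurrences.** The protocol gives no two-year rate. Its Discussion cites 20-30% recurrence within 12 months in a study of oral tongue cancer.
- If nobody recurred after month 12: 97 × 0.20 = 19 to 97 × 0.30 = 29 events.
- If the hazard stayed constant to month 24: 97 × (1 − 0.80²) = 35 to 97 × (1 − 0.70²) = 49 events.

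The 26 and 41 events used below lie between these extremes.

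**3. The two tests.** Let x be the grade (0 to 3). At each recurrence, compare the patient's x with the mean of x among those still at risk.
- Trend: U = Σ(xᵢ − x̄ at risk), V = Σ(variance of x at risk). U²/V is referred to chi-square on 1 degree of freedom. This is also the score test of a Cox model with grade as a number.
- Four-group log-rank: the same construction with three grade indicators, UᵀV⁻¹U, on 3 degrees of freedom.

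**4. Power when risk rises with grade.** All settings are assumptions: four grades, exponential recurrence times, censoring at 24 months, two-sided 5%, hazard ratio 1.5 per grade. The last three rows are a separate set of runs with equal-sized grades, where the risk is the two-year risk at the middle of the scale.

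| Setting | Four-group log-rank | Trend |
|---|---|---|
| 97 patients, about 26 events | 44% | 60% |
| 97 patients, about 41 events | 64% | 79% |
| 97 patients, 30% risk | 52% | 69% |
| 97 patients, 40% risk | 64% | 80% |
| 60 patients, 30% risk | 33% | 47% |

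The gain is 14 to 17 points throughout. With no true effect and 97 patients, both tests stayed near 5% (trend 4.6-5.4%, four-group 5.2-5.3%).

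**5. Power when the effect is a step.** If only the top grade differs, or only any staining against none, the trend test loses about 3-10 points against the four-group test. If the step lies in the middle of the scale, it gains about 3-7 points.

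**6. Presence or count for CTC.** Again under assumptions, with 97 patients:

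| True relation | Presence, log-rank | Log-count, Cox |
|---|---|---|
| Hazard ratio 1.3 per doubling of the count | 38% | 67% |
| Hazard ratio 2.5 for presence against absence | 64% | 42% |

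The ranking reverses with the assumed relation, so these figures do not show presence to be the wrong coding.

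**The case against.** **The trend test is itself a log-rank test, and a condensed article may leave the version to a fuller plan.** This is fair. The protocol does not exclude the trend version. But its section headed as the statistical analysis plan names its tests, and without the word trend the usual reading is the unordered comparison. The point is therefore a precise improvement to a stated choice. The named test remains valid.

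**The gain depends on a graded effect.** This also stands. With a hazard ratio of 2.5 confined to the top grade, a top-against-rest split fixed in advance had 78% power and the trend test 51%. That split wins only if its position is known beforehand, and the protocol offers no reason to expect one.

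**Three stronger readings are tempting and are not supported.**
- A reader might infer that the CTC coding contradicts itself, presence in the outcome and numbers in the methods. The numbers wording sits in the chi-square sentence on association with node expression. The survival outcome says presence, which is a yes/no grouping suited to a log-rank test.
- A reader might infer an inflated false-positive rate. Searching for the best cut would raise the nominal 5% to about 12-14% for four grades and 20-24% for CTC counts. The protocol proposes no such search, and a log-rank test across all grades needs no cut.
- A reader might infer that the protocol expects few recurrences. It gives no expected number.

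**Conclusion.** The point holds for the three tissue markers. The named comparison leaves the order of the grades unused unless the trend version is meant. If risk rises by about 1.5 per grade, power with 97 patients is about 44-64% for the four-group test and 60-79% for the trend test. The number of grades, their distribution, the effect size and the event count are all assumed. The price is about 3-10 points if the effect sits entirely at one end of the scale.

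The point does not extend to replacing presence by the CTC count as the main analysis. That is a trade-off which the documents do not settle. This is a worthwhile improvement and does not invalidate the planned analysis.

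**What to change.** In the Statistical method paragraph, state the following:

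- Each of STAT 3, LOX 2 and VEGF will be tested against recurrence-free survival with the log-rank test for trend across the intensity grades, or equivalently with a Cox model using grade as an ordered score.
- Kaplan-Meier curves will be shown for all grades. No high/low cut will be chosen from the outcome data.
- For CTC and CTM, the log-rank groups are presence against absence: at least one CTC, and at least one cluster. A Cox model on log2(CTC count + 1) is supporting only, and the text should say how each of the two sampling times enters it.

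The cost is a few sentences and no new data. The Study status section reports 27 patients recruited and marker standardization still under way, so at the time of writing the change could be made before any node marker was read. The downsides are that results are expressed per grade, and that effects confined to one end of the scale, or not monotone, are tested somewhat less well.

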### Methodological issues

•The study investigates the molecular characteristics of the premetastatic, metastatic lymph nodes in OTSCC related to the most suitable and real control group.•The CTC PMN association if present may help to correlate two triggering factors in overt metastasis formation.•The primary limitation of this study is the limited number of antibodies used to identify the molecular PMN characteristics. The study is aiming to co-relate the molecular markers of different possible events in organ remodelling and immature pre-metastatic niche formation. However, to get a wholesome picture of PMN features a greater number of antibodies to be included for evaluation. Due to budgetary constraints, we have limited our molecular markers by choosing the best which describe the maximum possible molecular events. Also, the lack of sequential blood evaluation for CTC in more frequent intervals will not allow us to comment on its time of appearance and its effect on metastasis accurately.CTC evaluation is based only on EpCAM and cytokeratin without considering the Epithelial-Mesenchymal Transition (EMT) mechanism, stemness characteristics or its subpopulations.

